### Adverse event reporting

Participants will have the opportunity to record any adverse events that occurred during trial at each weekly follow-up appointment. Any severe adverse events are recorded on a form on REDCap and reported to Monash Human Ethics. Non-serious events will be recorded on a REDCap form and in patient notes.

### Data analysis

Primary and secondary outcomes will be assessed between groups at the primary endpoint (week 4) using two-sample *t*-tests (if normally distributed) or Mann-Whitney *U* tests (if not normally distributed). In addition, variables with multiple time points will also be assessed using generalised linear mixed-effects models. Models will be adjusted for confounders such as age, sex, baseline depression/anxiety/stress, history of migraine or other comorbidities, and cardiovascular fitness (Godin assessment). Feasibility (recruitment, retention, and completion rates), adherence (proportion), and safety (number and types of adverse events) will also be assessed. A statistician will be consulted in the events of missing data, any additional analysis, and to advise on interim analyses and stopping guidelines. Participants who do not complete the full 4-week intervention (i.e. lost to follow-ups) will be excluded from the primary endpoint analysis however will be retained in the descriptive analyses of the feasibility outcomes. Only the principal investigator will have the authority to terminate the trial.

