**Methods:**

The target sample size of 120 women (aged 18–70) with a history of IPV (last instance > 3 months ago) and probable PTSD (via the PTSD Checklist for DSM-5; PCL-5) will be recruited via community advertisement in Melbourne, Australia. The trial will be completed at the Alfred Centre, Monash University. Participants will complete an exercise tolerance test via the Buffalo Concussion Bike Test and then will be randomised into either aerobic exercise or passive stretching. Participants will be instructed to complete 20 min of allocated aerobic exercise or stretching for 4 weeks and given a written diary and a Fitbit smartwatch to track program adherence. The primary outcome, PTSD symptoms via the PCL-5, will be collected at baseline, 1, 2, 3, and 4 weeks (primary endpoint). Secondary outcomes, including additional determinants of health (i.e. sleep, pain, substance use), cognitive testing, concussion-like symptoms in participants with a history of IPV-related brain injury, blood-based biomarkers, and feasibility and adherence to the prescribed program, will also be collected weekly at baseline, 1-, 2-, 3-, and 4-week follow-ups.

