### Population

Women aged 18–70 with a history of IPV (last instance > 3 months ago) and probable PTSD (via the PTSD Checklist for DSM-5; PCL-5) will be recruited.

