## Outcomes

### Primary outcome

The primary outcome of this trial is PTSD symptom burden measured by the PTSD Checklist for DMS-5 (PCL-5) (Table 1). The PCL-5 is a validated and reliable survey for measuring severity of PTSD symptoms and has been used to measure symptom burden in IPV victim-survivors in previous studies [28–30]. The PCL-5 is composed of 20 questions to determine how much a participant was bothered by common PTSD symptoms in the past 3 months. Each question/symptom is ranked on a five-point Likert scale from “0”—not at all to “4”—extremely, with the highest possible value being 80. Probable PTSD was described as a PCL-5 score of >31.

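### The week-4 primary comparison of PCL-5 is an unadjusted test chosen by normality, which leaves the collected baseline PCL-5 unused and costs power

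*Protocol article*

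**What the plan says.** The Primary outcome section names the measure: "The primary outcome of this trial is PTSD symptom burden measured by the PTSD Checklist for DMS-5 (PCL-5"). The abstract gives its schedule: "The primary outcome, PTSD symptoms via the PCL-5, will be collected at baseline, 1, 2, 3, and 4 weeks (primary endpoint"). Table 2 agrees, with PCL-5 at day 0, days 7, 14 and 21, and day 28.

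The Data analysis section then sets the between-group comparison: "Primary and secondary outcomes will be assessed between groups at the primary endpoint (week 4) using two-sample" t-tests, or "Mann-Whitney *U* tests (if not normally distributed"). It mentions no baseline term, covariate or change score for this comparison.

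A second analysis follows: "In addition, variables with multiple time points will also be assessed using generalised linear mixed-effects models". Its covariates are introduced as examples: "Models will be adjusted for confounders such as age, sex, baseline depression/anxiety/stress, history of migraine or other comorbidities, and cardiovascular fitness (Godin assessment"). Baseline PCL-5 is not among them. Sex is, although the Population section restricts entry to women: "Women aged 18–70 with a history of IPV (last instance > 3 months ago").

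The Design and Trial allocation sections specify simple 1:1 randomisation, with no stratification described.

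**The concern.** Baseline severity usually explains part of the variation in a later score on the same scale. A test of raw week-4 scores leaves that variation in the error term, so the trial is less likely to detect a real effect than its own data would allow. Simple randomisation does not balance baseline PCL-5 by design, and an unadjusted test makes no correction for whatever chance difference arises. The same rule is applied to the secondary outcomes, many of which also have a baseline value.

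The normality rule is a separate weakness. A t-test goes with a difference in mean PCL-5 points. A Mann-Whitney test concerns the ordering of scores between arms and yields no mean difference. If the observed distribution decides between them, the quantity that the trial reports is not fixed in advance.

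**Working it through.** **Inputs from the protocol article**
- Sample size section: earlier trials of 46 to 96 participants, 20% drop-out, target 120.
- Data analysis section: participants who do not complete the 4 weeks are left out of the primary endpoint analysis.

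**Inputs assumed**
- A two-sided 5% level, a true difference of 0.5 SD, and a baseline to week-4 correlation r of 0.3 to 0.7. The article states none of these.

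**Step 1. The plan's own figure.** 96 / (1 − 0.20) = 120, so the target equals the upper end of the earlier trials inflated for drop-out. The number analysed is then about 120 × 0.80 = 96, or 48 per arm. The article gives no effect size, SD or power, so there is no power figure to reproduce.

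**Step 2. Unadjusted week-4 t-test.** The noncentrality is 0.5 × √(48/2) = 2.449 on 94 degrees of freedom. Power is 67.9%. (A normal approximation gives 68.8%.)

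**Step 3. Adjustment for baseline PCL-5.** Residual variance falls by the factor 1 − r², so the standardised difference becomes 0.5 / √(1 − r²). The unadjusted sample needed to match 96 adjusted participants is 96 / (1 − r²). One degree of freedom for the covariate is ignored here.

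| r | 0.5/√(1 − r²) | Power | 1/(1 − r²) | Matching unadjusted total |
|---|---|---|---|---|
| none used | 0.500 | 67.9% | 1.00 | 96 |
| 0.3 | 0.524 | 72.0% | 1.10 | 105 |
| 0.4 | 0.546 | 75.3% | 1.19 | 114 |
| 0.5 | 0.577 | 79.9% | 1.33 | 128 |
| 0.6 | 0.625 | 85.8% | 1.56 | 150 |
| 0.7 | 0.700 | 92.4% | 1.96 | 188 |

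**Step 4. Detectable difference at 80% power (normal approximation).** Unadjusted: (1.960 + 0.842) × √(2/48) = 0.57 SD. Multiplying by √(1 − r²) gives 0.55 SD at r = 0.3, 0.50 SD at r = 0.5 and 0.41 SD at r = 0.7.

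**Step 5. Chance baseline difference.** Its standard error is √(2/48) = 0.204 SD, so a gap of at least 0.2 SD in either direction has probability 33%. With equal SDs, such a gap shifts the expected week-4 difference by r times its size: at r = 0.5, 0.5 × 0.2 = 0.1 SD.

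**Step 6. Would a change score do instead?** Its SD is √(2(1 − r)) in units of the week-4 SD. At r = 0.3 that is 1.18, and the detectable difference becomes 0.57 × 1.18 = 0.68 SD, worse than the raw week-4 test. It breaks even at r = 0.5 and does not beat ANCOVA at any r in this range.

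**The case against.** The strongest reply is that nothing here makes the result wrong, and that stands. Under randomisation the unadjusted test keeps its type I error and is unbiased. Chance baseline differences are already reflected in its standard error. A reader might infer that such a difference passes in full into the week-4 result; Step 5 shows that it carries over only in proportion to r.

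The size is also open to challenge. Neither 0.5 SD nor r comes from the article. Entry requires a PCL-5 above 31, which narrows the baseline range and may lower r. At r = 0.3 the gain is only about four percentage points, so the 92% figure is a favourable case. This stands too, and is why a range is shown.

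Three further readings are tempting but not supported:
- **That the mixed model excludes baseline PCL-5.** The covariate list is open, and the model may take baseline as its first time point. Baseline PCL-5 is unnamed, not ruled out, and its handling may be settled in an analysis plan that is not shown.
- **That the two analyses have no order.** The two-sample test is tied to the primary endpoint and the models are introduced as additional, which implies precedence.
- **That the trial will adjust for activity measured after randomisation.** Table 2 repeats the Godin questionnaire weekly and the covariate list does not tie it to baseline, so the wording allows this. It does not state it.

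None of these replies changes the week-4 test itself, which the article does specify.

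**Conclusion.** The point holds as one of efficiency and of a data-dependent effect measure. It should be fixed, but it does not threaten validity. Under the stated assumptions, the planned test has 68% power where a baseline-adjusted analysis of the same participants would have 72% to 92%. That is equivalent to an unadjusted sample 1.10 to 1.96 times as large. The direction of the gain does not depend on the assumed effect, but its size depends on r, which the article does not give.

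The listing of sex is a drafting slip with no numerical effect, since a constant drops out of the model. It should not be read as evidence that the analysis is unsound.

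**What to change.** Name one primary analysis: a baseline-adjusted comparison of week-4 PCL-5, reported as a mean difference with 95% CI. Either of two forms would serve:
- ANCOVA of week-4 PCL-5 on group and baseline PCL-5; or
- a mixed model for repeated measures with baseline PCL-5 and a week-4 treatment contrast.

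Remove the rule that switches to Mann-Whitney on observed normality. For secondary outcomes measured only at baseline and day 28, such as the repeated cognitive tests, WHOQOL-BREF and ITQ, use ANCOVA on the baseline value.

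As minor tidying, delete sex from the covariates and state that Godin and the other covariates are baseline values.

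The cost is wording in the protocol and the analysis plan. Every variable needed is already scheduled in Table 2. Data collection is expected to run to 16/05/2027, so the change can still be made before the final analysis.

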### Objectives

The primary objective is to determine the effects of a 4-week program of structured aerobic exercise on PTSD symptom burden in women IPV victim-survivors compared to those who complete a program of 4 weeks of passive stretching. The secondary objective is to determine the effects of the exercise intervention on biopsychosocial measures (i.e. quality of life, depression, anxiety and stress, concussion-like symptoms, sleep), cognitive performance, and blood biomarkers related to inflammation and growth factors compared to passive stretching.

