### Sample size

Although there are limited studies to base a statistical power calculation, the sample size was determined based on previous sample size estimates from trials using sub-symptom threshold aerobic exercise (STAE) interventions, which ranged from 46 to 96 participants [20, 21]. With an estimated drop-out rate of 20%, we will aim to recruit 120 participants [21].

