## Data collection, management, and analysis

### Trial allocation

This study is an open-label study; therefore, the investigator, site staff, and subjects will not be blinded to treatment allocation. A computer-generated randomisation schedule will be prepared by a statistician prior to the start of the study. Treatment allocation will be made per the randomisation list. After signing the informed consent form, subjects will be allocated a unique subject ID and administered the screening instruments via Research Electronic Data Capture (REDCap). A unique subject ID will be used to identify the subject throughout the study period and on all study-related documentation. After eligibility has been established, subjects will complete all baseline assessments followed by a simple randomisation in a 1:1 ratio to either the aerobic exercise or stretching group. Randomisation will be allocated sequentially based on the pre-determined randomisation schedule and according to their chronological order of inclusion in the study.

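### The primary week-4 PCL-5 test is a t-test or a Mann-Whitney test depending on the observed distribution, so the primary effect measure is not fixed in advance

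*Protocol article*

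**What the plan says.** The Objectives section gives the aim without an effect measure: "The primary objective is to determine the effects of a 4-week program of structured aerobic exercise on PTSD symptom burden", compared with stretching. The Primary outcome section defines the PCL-5 total as 20 items scored 0 to 4, "with the highest possible value being 80".

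The Data analysis section then sets the test: "Primary and secondary outcomes will be assessed between groups at the primary endpoint (week 4) using two-sample" t-tests when the data are normal, and Mann-Whitney U tests when they are not ("if normally distributed) or Mann-Whitney"). One rule covers primary and secondary outcomes. A second method follows: "In addition, variables with multiple time points will also be assessed using generalised linear mixed-effects models". PCL-5 is collected weekly, so this model applies to it, but the wording makes it an addition to the week-4 test and does not designate it primary.

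The Trial allocation section describes an open-label trial with "simple randomisation in a 1:1 ratio".

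**The concern.** The week-4 distribution is known only after outcomes are in, so the choice between the two branches is made then. The branches answer different questions. The t-test concerns the difference in mean PCL-5. Mann-Whitney concerns whether a woman in one arm tends to score higher than a woman in the other. A reader of the protocol cannot tell which of these the trial will report as its primary result.

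Three things are at stake:

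- the primary result may come without a size in PCL-5 points;
- the verdict at 5% may depend on which branch was taken;
- staff who know the allocation will be making, or supplying, a judgement about normality that decides the primary test.

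**Working it through.** **Inputs.** From the Sample size section: earlier trials "which ranged from 46 to 96 participants", and "With an estimated drop-out rate of 20%, we will aim to recruit 120 participants". The upper figure reproduces the target: 96 / (1 − 0.20) = 120. Non-completers are excluded from the primary endpoint analysis, so 120 × 0.80 = 96 are expected, or 48 per arm at 1:1 (simple randomisation will not give exactly equal arms).

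**Assumptions, none from the document.** Two-sided 5%; normality judged by Shapiro-Wilk at 5% in each arm, with Mann-Whitney used if either arm fails; scores drawn from the shapes below, rounded and clipped to 0-80. Each scenario had 4,000 or 10,000 simulated trials.

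**What each branch estimates.** The t-test targets mean(exercise) − mean(stretching), in PCL-5 points. Mann-Whitney targets P(X > Y) + ½P(X = Y), a probability. The two coincide in verdict only under further assumptions, such as a pure shift.

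**Does the comparison of means need normal scores here?** With 48 per arm and identical distributions, Welch's t-test rejected 5.1% (normal), 5.2% (bounded, 80 × beta(2,3)), 4.9% (gamma(8,4)), 5.5% (gamma(4,8)) and 4.8% (two-group mixture). It is valid across these shapes. The detectable standardised difference at 80% power is (1.960 + 0.842) × √(2/48) = 0.57, or 0.57 × 15 ≈ 8.6 points if the SD is 15 (assumed).

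**How predictable is the branch?** With no effect, Mann-Whitney was chosen in 7% of trials with normal data, 36% with the bounded beta, 65% and 85% with the two gamma shapes, 67% with the mixture, and 92% with a strongly skewed score (mean 30, SD 16).

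**Error rate of the switching rule when both arms share one distribution.** 5.1% with normal data (mean 35, SD 15) and 5.1% with skewed data (mean 30, SD 16). Gamma(8,4), gamma(4,8) and the bounded beta gave 5.0%, 4.9% and 5.4%. The two tests disagreed in about 2% of the null trials in the first two cases.

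**Power and disagreement with a true effect.** Rows 1-3 use the equal-variance t-test and the others Welch's; with equal arms the two are practically the same.

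| Scenario | t-test % | Switching rule % | Difference | Tests disagree % |
|---|---|---|---|---|
| 1. Normal, 35 v 27, SD 15 | 73.1 | 72.9 | −0.2 | 5.4 |
| 2. Both skewed, 32 v 24, SD 16 | 69.7 | 79.3 | +9.6 | 11.6 |
| 3. Normal 35 (SD 15) v skewed 27 (SD 16) | 72.8 | 82.9 | +10.1 | 10.9 |
| 4. Gamma(4,8), pure 8-point shift | 67.8 | 73.5 | +5.7 | not recorded |
| 5. Gamma(8,4), pure 6-point shift | 73.1 | 75.6 | +2.5 | not recorded |
| 6. 80 × beta(2,3), 8-point shift | 67.0 | 65.7 | −1.3 | not recorded |
| 7. Gamma(4,8) v gamma(4,6) | 79.2 | 75.5 | −3.7 | not recorded |
| 8. 30% of women improve 22 points | 62.3 | 60.2 | −2.1 | 9.1 |

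Most differences are a few points, of either sign. The two near 10 points arise where the shapes of the arms differ as well as their means, so the rank test responds to more than the mean.

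**Similar means, different shapes.** With exactly equal means and 30% responders, the switching rule rejected 6.0% against 5.0% for Welch. With near-equal means and 30% responders it was 9.6% against 5.8%. In a deliberately extreme case (means 30.0 v 29.6, SD 8 normal v SD 20 skewed) it was 24.0% against 6.4%.

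**The case against.** The best defence is that both branches and the condition are named in advance, that the exact normality criterion may stand in an analysis plan not shown here, and that the procedure behaves well. Much of this stands. The missing criterion is not held against the article. The switching rule keeps close to 5% when the arms do not differ, and in several skewed scenarios it has more power than the t-test. What the defence does not reach is the rule itself: however normality is judged, a data-dependent choice between two effect measures remains.

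A reader might infer that the rule rejects too often. The documents and the calculations do not support that as a general claim. The excess appears only when exercise changes the shape of the distribution while the means stay equal or nearly so. Even then, rejection is a false positive only if the mean difference is already taken as the target, which the plan does not say. The 24.0% case was built to be extreme.

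A reader might also infer that the trial will report no PCL-5 point difference. That goes too far: the mixed model could supply one, and a Mann-Whitney result can be accompanied by a Hodges-Lehmann shift. Neither is the designated primary result.

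Finally, saying that the switch is useless would be wrong. It can gain power with skewed scores. It is simply not needed for a valid comparison of means.

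**Conclusion.** The point holds in a limited form and should be corrected before analysis. The plan lets the observed week-4 data decide whether its primary result is a mean difference or a rank comparison, and nothing else in the article settles the effect measure. In the scenarios with a true effect where agreement was recorded, the choice of branch would change the 5% verdict in roughly 5-12% of trials. Validity under no difference between the arms is not in doubt, and the power effect goes either way. All simulated figures rest on the assumed Shapiro-Wilk rule, the assumed shapes and SDs, and 48 completers per arm. That the effect measure is unfixed rests on the text alone.

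**What to change.** For the primary outcome, delete the normality condition and state one analysis: the difference between arms in mean PCL-5 at day 28, with 95% CI, from a linear model adjusted for baseline PCL-5, used whatever the observed distribution. Report Mann-Whitney with a Hodges-Lehmann shift as a sensitivity analysis, and say that the mixed model is supportive.

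PCL-5 is already collected at baseline and day 28, so the change needs no new data and leaves the target of 120 as it is. The Trial status section puts the end of data collection in May 2027, so an amendment can still precede the analysis. The price is some power relative to ranks if week-4 scores are strongly skewed: about 3 to 6 points for the pure shifts of skewed scores above, and up to about 10 where the shapes also differ. These figures are for the unadjusted t-test; adjusting for baseline PCL-5 should recover part of this, by an amount that depends on its correlation with week 4, which the article does not give.

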## Methods

### Design

This trial is an open-label randomised controlled superiority trial to compare the effectiveness of aerobic exercise to passive stretching in women victim-survivors of IPV with probable PTSD. Trial design is such that participants will be randomly allocated using simple randomisation (ratio 1:1) in parallel to either aerobic exercise intervention or control passive stretching intervention. This trial will be taking place at the Alfred Centre at Monash University in Melbourne, Australia. No patients or members of the public were involved in the design, conduct, or reporting of this protocol due to the sensitive nature of the study population.

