### Assessment and collection of outcomes

Participants will be assessed at baseline (day 0) and at the primary endpoint (day 28). During the trial, participants will return and be re-evaluated weekly on PTSD symptoms, BCBT, biopsychosocial questionnaires, and fluid biomarkers. In addition to exercise compliance, medications, and therapies, as well as any adverse events, compliance and feasibility will be evaluated at the weekly follow-up appointment. Cognitive assessment will only be repeated on the final evaluation. All data collection will occur at the Alfred Centre, Monash University. The full study schedule is included (Table 2).

**Table 2 Tab2:** Study schedule

Study assessments	Screening	Baseline	Intervention period	Weekly follow-up	Final visit
		Day 0	Day 1–6; day 8–13; day 15–20; day 22–27	Day 7, 14, 21	Day 28
Screening					
Eligibility questionnaire	X				
Enrolment					
Inclusion/exclusion criteria review	X	X			
Informed consent		X			
Allocate unique subject study identification		X			
Questionnaires					
Demographic data		X			
Medical history		X			
Ohio State University TBI Identification Method		X			
Godin Leisure-Time Exercise questionnaire		X		X	X
Medications		X		X	X
Current therapies		X		X	X
Exercise tolerance test					
Buffalo Concussion Bike Test (BCBT)		X		X	X
ECG recording		X		X	X
Biopsychosocial					
PTSD symptomology: PCL-5	X	X		X	X
Rivermead Post-Concussion Symptoms Questionnaire (RPQ)		X		X	X
Depression, Anxiety & Stress Symptom Scale (DASS-12)		X		X	X
The Alcohol, Smoking and Substance Involvement Screening Test (ASSIST-LITE)		X			X
Brief Pain Inventory (BPI)		X			X
12-Item Short Form Health Survey (SF-12)		X			X
World Health Organisation Quality of Life (WHOQOL-BREF)		X			X
Sleep-related inventory (SRI)		X			X
International Trauma Questionnaire (ITQ)		X			X
Neuropsychological assessment					
TOPF		X			
RAVLT		X			X
Digit Span		X			X
O-SDMT		X			X
TMT		X			X
Biomarkers					
Blood sample collection		X		X	X
Therapeutic intervention					
Dispense intervention		X		X	
Fitbit—dispense and instructions		X			
Record daily intervention sessions			X		
Return of Fitbit					X
Safety and feasibility assessments					
Adverse event monitoring		X		X	X
Feasibility					X

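### The primary week-4 PCL-5 test makes no use of the day-0 PCL-5 collected before randomisation; the test is valid but gives up precision that costs nothing to keep

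*Protocol article*

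**What the plan says.** Data analysis fixes the main comparison: "Primary and secondary outcomes will be assessed between groups at the primary endpoint (week 4) using two-sample" t-tests, or Mann-Whitney U tests if the data are not normal. It does not say that these tests are run on change from baseline.

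A second analysis follows: "In addition, variables with multiple time points will also be assessed using generalised linear mixed-effects models". Its covariates are given as examples: "Models will be adjusted for confounders such as age, sex, baseline depression/anxiety/stress, history of migraine or other comorbidities, and cardiovascular fitness (Godin assessment".

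The baseline score exists. The abstract states: "The primary outcome, PTSD symptoms via the PCL-5, will be collected at baseline, 1, 2, 3, and 4 weeks (primary endpoint"). Table 2, in the row "PTSD symptomology: PCL-5", marks it at screening, day 0, the weekly visits and day 28. Trial allocation places all baseline assessments before randomisation.

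The Design section says participants are "randomly allocated using simple randomisation (ratio 1:1) in parallel", with no stratification. The Population section restricts entry: "Women aged 18–70 with a history of IPV".

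**The concern.** A patient's own starting score usually carries information about her score four weeks later. A two-sample test on week-4 values leaves that information in the error term, so the interval for the treatment effect is wider than it need be. With unstratified allocation, a chance difference in starting severity is neither prevented by the design nor corrected in the test.

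This matters more here because the Sample size section contains no power calculation. The target comes from the sizes of earlier trials, so no margin of power has been shown that would make the lost precision harmless.

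The point concerns a method that the protocol states, not a detail left to an analysis plan. A plan that made a baseline-adjusted analysis primary would depart from this text.

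**Working it through.** **Analysed number.** The Sample size section cites trials of 46 to 96 participants and 20% dropout. 96 / (1 − 0.20) = 120 reproduces the stated target. Data analysis excludes non-completers from the primary endpoint analysis, so about 120 × 0.80 = 96 women are analysed, or 48 per arm (simple randomisation makes this approximate). There is no power figure in the protocol to reproduce.

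**Assumptions.** Two-sided 5%, 80% power, equal SDs at day 0 and day 28, a t-test rather than a Mann-Whitney test, and a day-0 to day-28 correlation r of 0.3 to 0.7. The protocol gives none of these values.

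**Unadjusted test.** The standard error of the difference is √(2/48) = 0.204 SD. Solving the noncentral t distribution with 94 degrees of freedom for 80% power gives 0.578 SD. The normal approximation gives (1.960 + 0.842) × 0.204 = 0.572 SD.

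**Baseline-adjusted analysis.** The residual SD is multiplied by √(1 − r²), and so is the detectable effect. The equivalent number of women analysed without adjustment is 96 / (1 − r²).

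| Assumed r | √(1 − r²) | Detectable effect (SD) | Equivalent women | Power at a true 0.5 SD |
|---|---|---|---|---|
| unadjusted | 1.000 | 0.578 | 96 | 68% |
| 0.3 | 0.954 | 0.551 | 105 | 72% |
| 0.4 | 0.917 | 0.530 | 114 | 75% |
| 0.5 | 0.866 | 0.500 | 128 | 80% |
| 0.6 | 0.800 | 0.462 | 150 | 86% |
| 0.7 | 0.714 | 0.413 | 188 | 92% |

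**Simulation check.** In 4,000 runs per setting with a true 0.5 SD effect, power for the t-test against ANCOVA was 68% v 71% (r = 0.3), 67% v 79% (r = 0.5) and 67% v 91% (r = 0.7). With no true effect, both methods rejected in about 5% of runs (range 4.4% to 5.6%).

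**Chance imbalance.** The difference in day-0 means also has a standard error of 0.204 SD. It reaches the week-4 difference multiplied by r: 0.06, 0.10 or 0.14 SD per standard error of imbalance at r = 0.3, 0.5 or 0.7. The unadjusted standard error already contains this variation, so it is another view of the same loss and not a second one.

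**Change scores are no safe substitute.** The variance of a change score is 2(1 − r) times the week-4 variance: 1.4 times at r = 0.3, equal at r = 0.5, and 0.6 times at r = 0.7, where ANCOVA has 0.51.

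**The case against.** *The unadjusted test is valid.* This stands. Before any exclusions it is unbiased under randomisation, and the simulation shows the nominal error rate. A reader might infer that the primary result would be biased, or that any baseline imbalance passes in full into the estimate. Neither follows: the imbalance is scaled by r, and the test's standard error already allows for it.

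*The mixed model may use the baseline anyway.* This stands too. A reader might infer from "Models will be adjusted for confounders such as age, sex, baseline depression/anxiety/stress" that the models discard day-0 PCL-5. The text does not support that. The covariates are offered as examples, and PCL-5 at day 0 may be one of the repeated responses, in which case leaving it off the covariate list is right. Baseline depression, anxiety and stress may also recover some precision. But the protocol presents the models as an addition to the week-4 test, so they do not repair the primary comparison.

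*The gain is unknown and may be small.* This stands in part. Entry requires a PCL-5 above 31 on a scale to 80, which narrows the baseline range and may lower r. At r = 0.3 the gain is modest: 0.58 to 0.55 SD.

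*Sex in the covariate list is trivial.* Agreed. A constant term drops out and does no numerical harm.

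**Conclusion.** The point holds for the primary week-4 comparison. As stated, that test makes no use of a pre-randomisation PCL-5 score that every participant will have. The harm is lost precision and uncorrected chance imbalance, not invalidity.

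Under the assumptions listed, the reduction in detectable effect forgone runs from about 5% (r = 0.3) to about 29% (r = 0.7), that is, 1 − √(1 − r²). In terms of information, the trial gives up the equivalent of about 9 to 92 further women beyond the 96 analysed. The lower part of the range may be the more realistic, given the entry cut-off. Whether the additional mixed model loses the same information cannot be determined from the protocol.

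This should be fixed as a free improvement. It is not a fault that would invalidate the trial.

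**What to change.** Name one primary estimate: the day-28 difference in mean PCL-5 between arms, adjusted for day-0 PCL-5, from ANCOVA or as the day-28 contrast of the mixed model.

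For the mixed models, state how each outcome's own day-0 value enters. It can be a covariate, with the post-baseline visits as responses, or a response with day-0 means set equal across arms, but not both. The distinction also settles the depression, anxiety and stress outcome, whose baseline is already on the covariate list.

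Delete sex from the list as a tidy-up.

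The cost is a few sentences in Data analysis, handled as a protocol amendment. No visits, measurements or participants are added. Trial status reports recruitment as ongoing at submission, with data collection expected to end in May 2027, so the change can be specified before the final analysis.
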